#### Plan to share and analyze data

A clinical trial evaluating the effects of a preoperative balance training which is supervised in the hospital versus a conventional preoperative training is being conducted in parallel at the Hospital Clínico y Universitario of Valencia (NCT-02995668). The design of the experimental intervention coincides with that of this work. For this reason, and if the 2 trials are successfully completed, we plan to share the data in order to compare the matching interventions (PRE_EXP1 versus PRE_NA). The analysis shall take into account the center effect or correlation between the data, which will be evaluated as intraclass correlation coefficients. Since the idea is to extend the results to the centers that are concerned by the experimental treatment, the analysis of data will involve a mixed effects regression model, and treatment condition, covariates and other cofounding factors may be included as fixed effects [33]. The combination of data from the experimental groups will make it possible to consider the potential influences due to the center effect, and is expected to provide results of greater consistency, external validity and generalizability [34].

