#### In-hospital supervised preoperative intervention (PRE_ EXP1)

Different exercises are proposed and developed over the course of the 12 sessions on alternate days, divided in 4 weeks of training. On the one hand the intervention includes a standard program of rehabilitation with strengthening exercises. In addition, each session includes a total of 4 to 5 balance and proprioceptive exercises performed over a period of 20 min. The training has been based on the Fitzgerald principles to train proprioception, on previous of our works, and on clinical experience [21, 23]. The first 2 weeks are oriented to enhance balance and proprioception with the side, treadmill, cross, and tandem walk exercises. These exercises are excluded in weeks 2 and 3 and multiple changes of direction, foam activities and balance work with the Bohler plate are performed instead. Also 5 min training of weight bearing and testing the limits of stability are performed during the last 4 sessions. Progression in the exercises is implemented as tolerated, always trying to avoid fatigue. The physiotherapist is responsible for recording attendance at rehabilitation sessions.

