#### Non-active preoperative intervention (PRE_NA)

In order to evaluate the true effect produced by the interventions, and to determine whether the postoperative results obtained are due to the appropriateness of the proposals, a non-active control group (third arm) was added.

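### The pooling plan calls PRE_EXP1 versus PRE_NA common to two trials, but by its own description only the experimental arm matches

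*Protocol article*

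**What the plan says.** The protocol article, under Plan to share and analyze data, describes a parallel trial at another Valencia hospital that compares "a preoperative balance training which is supervised in the hospital versus a conventional preoperative training". It states one point of agreement between the trials: "The design of the experimental intervention coincides with that of this work". From this it concludes that, if both trials finish, "we plan to share the data in order to compare the matching interventions (PRE_EXP1 versus PRE_NA").

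For the analysis it says: "The analysis shall take into account the center effect or correlation between the data, which will be evaluated as intraclass correlation coefficients". It then names a mixed effects regression in which treatment condition and covariates may enter as fixed effects. The levels of treatment condition are not defined. The paragraph ends by expecting the combined data to give more consistent and more generalisable results.

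In this trial PRE_NA is the arm of which the article says "a non-active control group (third arm) was added". Table 1 gives it conventional physiotherapy after surgery and nothing before. The abstract says this comparator is there to separate the effect of training from the benefit of surgery alone.

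**The concern.** The contrast named for pooling needs both arms in both trials. As the paragraph describes them, the two trials share PRE_EXP1 only. One control is no preoperative training; the other is an active preoperative programme.

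The two contrasts therefore answer different questions. PRE_EXP1 has a conventional component: "On the one hand the intervention includes a standard program of rehabilitation with strengthening exercises". The balance exercises are added to it. Against PRE_NA, the comparison is with no preoperative training at all. Against conventional training, it is with another active programme. If the two are combined as one effect labelled PRE_EXP1 versus PRE_NA, a reader would take the result as the effect against no training. It would be a blend, and it would be presented as the stronger of the available results.

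**Working it through.** **1. The statements side by side**

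| Item | This trial | Parallel trial, as described |
|---|---|---|
| Experimental arm | PRE_EXP1 | Said to coincide with PRE_EXP1 |
| Control before surgery | None (Table 1; PRE_NA section) | Conventional preoperative training |
| Contrast available | PRE_EXP1 vs none | PRE_EXP1 vs conventional |

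The label PRE_EXP1 versus PRE_NA fits the first column only.

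**2. Inputs**

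- From Sample size: Berg score 53 with preoperative intervention, 5 points above the non-intervention group. So the control is 53 - 5 = 48. The protocol gives no figure for the pooled analysis.
- Assumed, not in the documents: conventional training gains c Berg points over none (c = 0 to 5); the effect of PRE_EXP1 over none is 5 points at both hospitals; this trial has weight w in the pooled estimate (the other trial's size is not given).

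**3. Pooled effect if both controls carry one label**

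- Contrast in this trial: 53 - 48 = 5
- Contrast in the other trial: 53 - (48 + c) = 5 - c
- Centre-adjusted pooled effect: 5w + (1 - w)(5 - c) = 5 - (1 - w)c
- With w = 1/2: 5 - c/2

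| c | w = 1/3 | w = 1/2 | w = 2/3 |
|---|---|---|---|
| 0 | 5.0 | 5.0 | 5.0 |
| 2 | 3.7 | 4.0 | 4.3 |
| 4 | 2.3 | 3.0 | 3.7 |
| 5 | 1.7 | 2.5 | 3.3 |

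Fitting a two-level treatment model with a centre term to the four cell means (53, 48, 53, 48 + c) gives the same equal-weight results: 5.0, 4.0 and 3.0 for c = 0, 2 and 4. The centre term is already in that model and does not remove the blend. Under these assumptions, the pooled effect equals the PRE_EXP1 versus PRE_NA effect only if c = 0.

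**4. What the four cells can and cannot separate**

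- *Three treatment levels (PRE_EXP1, PRE_NA, conventional) plus centre:* 4 parameters, rank 4, so estimable. The centre effect is the difference between the two PRE_EXP1 groups. The PRE_NA effect comes from this trial's two arms, and the conventional effect from the other trial's two arms.
- *The same model plus a treatment-by-centre term:* 5 parameters, rank 4, so not estimable. A different treatment effect between hospitals cannot be told apart from a different control.
- *Between-centre variation:* two centres leave 2 - 1 = 1 degree of freedom, so an intraclass correlation is barely estimable.

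**The case against.** Several points on the other side carry weight.

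- **The pooling is conditional and supplementary.** It is not among the trial's primary or secondary analyses. It does not touch the sample size, this trial's randomised comparisons or the economic evaluation. This stands and limits the severity.
- **Merged coding is not stated.** Nowhere does the article say that conventionally trained patients will be coded as PRE_NA. It also speaks of combining the experimental groups, and a three-level factor would be compatible with the text. This stands in part. Defining factor levels can be left to an analysis plan, but the article does name a single two-arm contrast and calls it matching. One label for both controls is the natural reading, though not a written rule.
- **Centre and control type are not inseparable.** A reader might infer that, with each control at one hospital only, no centre term could separate them. That is too strong. PRE_EXP1 is given at both hospitals, so three treatment levels plus centre can be estimated. Only the treatment-by-centre interaction is aliased with control type.
- **The other trial is known from one clause.** A reader might conclude that it certainly has no untreated arm. The article does not show its full arm structure. What can be said is that the article's description and its label disagree.
- **The size is not fixed.** The value of c and the weights are assumptions, and the range includes no distortion at all. Nor should a one-degree-of-freedom chi-square interval be offered as a confidence interval for the between-centre variance, because the variation between observed centre means also contains sampling error within centres.
- **Generalisability.** The article may mean extension to the participating centres only. This reading is possible, so the claim needs tempering rather than outright rejection.

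**Conclusion.** The contradiction holds on the article's own text and needs no assumption: only the experimental arm is described as common, yet the contrast with PRE_NA is called matching. The consequence depends on the coding. If both controls go under one label, the pooled effect is 5 - c/2 Berg points with equal weights, from 5.0 at c = 0 to 2.5 at c = 5. This rests on the protocol's 5-point effect applying at both hospitals and on the assumed c. The planned centre effect or intraclass correlation does not repair it.

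The documents do not support the stronger inference that this trial's own results are compromised. Within each trial the randomised contrast remains valid. This should be fixed before any data are shared, but it is not a critical flaw of the trial.

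**What to change.** Revise the paragraph as follows.

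1. State that only PRE_EXP1 is common to the two trials. If the other trial does have a non-active arm, say so and reconcile the description of its control.
2. Code treatment as three levels (PRE_EXP1, PRE_NA, conventional training), with trial/centre as a fixed effect.
3. Take PRE_EXP1 versus PRE_NA from this trial's randomised patients, and PRE_EXP1 versus conventional training from the other trial's.
4. Label any comparison of conventional training with none as indirect, through PRE_EXP1, and state its assumption of no treatment-by-centre interaction.
5. Drop the intraclass correlation and temper the statement on generalisability.

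The cost is a change of wording. The downside is that pooling then adds little precision to PRE_EXP1 versus PRE_NA, so the combined analysis has to be described more modestly.

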### Data analysis

The implementation of protocols will be presented with descriptive statistics. In an exploratory way, the drop-out ratios will be estimated and the survival analyses will be used [29]. This aspect will also be taken into account throughout the follow-up and registering when drop-outs occur. The incidence of adverse effects at 6 weeks will be evaluated, which will be categorized according to whether they are considered to be definitive, probable or possibly related to the interventions.

It is hypothesized that the experimental groups will have enhanced balance abilities, which may also have a direct impact on functionality in the short and mid-term. All temporal instants are of interest, although particular attention will be paid to the early postoperative effects (6w) and maintenance of potential mid-term benefits (1y).

The data analysis will include the sample descriptors, a comparison of the baseline condition with the t tests that will be parametric or not depending on the results of the tests of Wilcoxon and Shapiro-Wilk, and a comparison of the progress due to the results of the intervention with an ANOVA analysis of repeated measures, looking for interactions initially as a function of time, group, and time per group. In case of baseline differences between the participants, an ANCOVA analysis will be conducted instead, in which the data will be adjusted to the baseline scores. Analyses will be performed for primary and secondary outcomes. Post-hoc analyses will be performed accordingly. The significance levels will be set at 95%.

A qualitative analysis will be carried out in which it will be estimated if the obtained progressions measured as the mean values of the difference between the basal and final values for each variable at each time point reach the minimum established according to the psychometric properties referring to the minimum clinical importance difference or minimum detectable change with a CI of 95%, if they are available in the literature. If they had been reported by different studies, it would be based on the suggested minimum value.

A post-hoc power analysis and an estimate of the effect size will be implemented with the tool G*Power [20], based on Cohen’s *d* and considering a low, medium or high effect as a function of the result [30].

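### Two hospitals give one degree of freedom for the centre effect, so the planned ICC is nearly uninformative and the pooled model cannot carry the result beyond those two hospitals

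*Protocol article*

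**What the plan says.** The section Plan to share and analyze data describes a second trial, running at another hospital in Valencia, whose experimental arm coincides with the in-hospital arm here. The plan is: "if the 2 trials are successfully completed, we plan to share the data in order to compare the matching interventions (PRE_EXP1 versus PRE_NA").

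The clustering is handled as follows: "The analysis shall take into account the center effect or correlation between the data, which will be evaluated as intraclass correlation coefficients". The choice of model is justified by its target, "Since the idea is to extend the results to the centers that are concerned by the experimental treatment", and then "the analysis of data will involve a mixed effects regression model, and treatment condition, covariates and other cofounding factors may be included as fixed effects". The section closes with the expectation that combining the data "is expected to provide results of greater consistency, external validity and generalizability".

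No third centre is mentioned. The random terms are not listed. Centre as the random factor follows from the ICC, the mixed model and the stated reason taken together. The section does not restrict the conclusion to the two hospitals.

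**The concern.** A random centre term lets a result speak for centres that were not sampled only if the sampled centres show how much centres differ. Two centres give a single difference, which is one degree of freedom.

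Two consequences follow. First, the ICC is a poor measure of the centre effect here. It will often come out as zero when centres do differ, and a reader could take that zero as evidence of no centre effect. Second, a random centre intercept with a purely fixed treatment effect tests the average effect in these two hospitals. If the treatment effect itself differs between centres, that variation does not enter the standard error, and the interval is too narrow for an effect meant to hold across centres. The claimed gain in generalizability would then rest on a property that the design does not have.

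This is separate from the question of whether the control arms match. It would remain if they did.

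**Working it through.** The article gives no sample size, power or error rate for the pooled analysis, so there is no figure of its own to reproduce.

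**Inputs from the article**
- Centres: 2 (Plan to share and analyze data).
- Alpha: 0.05 (Sample size). Two-sided testing is assumed.
- Evaluable patients per group in this trial: 20, from 25 recruited, since 75/3 = 25 (Sample size).
- SD of the Berg Balance Scale: 4.5 points; expected difference 5 points (Sample size).

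**Assumptions, because the article gives no figure**
- Size of the parallel trial: 20 or 25 per arm, so m = 40 or 50 per centre.
- Both arms of the same contrast are present in each centre.
- True ICC: 0.05, with 0.01 and 0.10 as a range.
- Between-centre SD of the treatment effect, tau: 0 to 0.4 outcome SD.

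**1. Precision of a variance on 1 df.** The 95% limits are the estimate divided by the chi-square quantiles on 1 df, 5.024 and 0.000982. This gives 0.20 to 1,018 times the estimate.

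**2. Behaviour of the ICC.** With two centres of m patients, the one-way ANOVA ratio is distributed as theta × F(1, 2m − 2), with theta = 1 + m × ICC/(1 − ICC). The ICC estimate is (ratio − 1)/(ratio − 1 + m).
- For m = 40 and ICC = 0.05: theta = 1 + 40 × 0.05/0.95 = 3.105.
- Probability that the estimate is zero or negative: P(F(1, 78) ≤ 1/3.105 = 0.322) = 0.43.
- 97.5th percentile: ratio = 3.105 × 5.223 = 16.22, so the estimate is 15.22/55.22 = 0.28.
- At an average result (ratio = theta), the 95% interval for the ICC, cut at zero, runs from 0 to 0.99.
- For m = 50 the probability is 0.40 and the percentile 0.26.
- For m = 40 and true ICCs of 0.01 and 0.10, the estimate is zero or negative in 60% and 33% of cases.

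**3. Level of the test for the wider null.** In units of the outcome SD, with n per arm per centre, the model's variance for the pooled effect is (2/n)/2 = 1/n. If the effect varies between centres, the true variance about the all-centre mean is 1/n + tau²/2. The rejection rate of a nominal 5% test is 2 × (1 − Φ(1.96 × √[(1/n)/(1/n + tau²/2)])).

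Example with n = 20, tau = 0.2: 1/n = 0.05 and tau²/2 = 0.02; 1.96 × √(0.05/0.07) = 1.657, giving 9.8%.

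| tau (outcome SD) | n = 20 | n = 25 |
|---|---|---|
| 0 | 5% | 5% |
| 0.1 | 6% | 6% |
| 0.2 | 10% | 11% |
| 0.3 | 16% | 18% |
| 0.4 | 22% | 26% |

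On the Berg scale (SD 4.5, n = 20), tau = 1 point gives 10.9%. A simulation with a REML random-intercept model gave 4.8% at tau = 0 and 10.9% at tau = 1 point.

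**4. Does a richer model rescue the wider claim?** A test that treats the two hospital-specific effects as a sample of two uses t on 1 df, with critical value 12.71. It holds 5%. With 20 per arm per centre and a true difference of 5 Berg points, its power is 30%, 25% and 18% at tau = 0, 1 and 2 points. A random treatment-by-centre term tested with a Wald z gave simulated error rates of 3.7%, 7.4% and 15.0% at those values, with the variance estimated as zero in 68%, 59% and 44% of runs.

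**The case against.** Several counter-arguments have force.

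- **The target is partly inferred.** The article speaks of the centres concerned and never says other or further centres. Read narrowly, these could be the two hospitals themselves, and the planned test would then address its target. The stated expectation of external validity and generalizability points the other way, but it is a comparative claim, not a promise about all hospitals.
- **The model is partly inferred.** The random terms are not written out. A fixed treatment effect is compatible with an added random treatment-by-centre term, and an article may leave that detail to a fuller document. This stands, so the over-rejection figures apply only if no such term is fitted. The ICC and the reason given for the model are written out, and they do not depend on this.
- **The error rates are conditional.** A reader might infer that the pooled test simply over-rejects. The article does not support that. It gives no between-centre variation of the treatment effect, and without it the level stays near 5%. A badly estimated centre intercept does not by itself distort the treatment test when both arms are present in each centre.
- **The rates assume a shared contrast.** They need both arms in both hospitals. The parallel trial is described as training "supervised in the hospital versus a conventional preoperative training is being conducted in parallel", so no non-active arm is described there.
- **A fixed centre term alone changes little.** For the wider claim it has the same error rate as a random intercept. This is correct. What changes is the conclusion that the analysis is allowed to draw.

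**Conclusion.** The point holds in a limited form. With two hospitals the ICC is formally estimable but nearly uninformative, and no version of the mixed model gives usable support for a conclusion beyond these hospitals. Saying that the variance cannot be estimated at all would go too far.

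The ICC figures rest on an assumed true value and assumed centre sizes, although the single degree of freedom does not. The excess rejection, roughly 6% to 22% with 20 per arm per centre, rests on three further conditions: an assumed tau of 0.1 to 0.4 outcome SD, no random treatment-by-centre term, and the same randomised contrast in both hospitals. For the two-hospital average the test is sound.

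A reader might also infer that the trial's own results are at risk. They are not: the pooling happens only if both trials are completed, is supplementary, and leaves the primary comparisons within this trial untouched. Severity is minor.

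**What to change.** Revise the section Plan to share and analyze data as follows.

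1. Fit centre as a fixed effect with two levels.
2. Drop the ICC as the measure of the centre effect.
3. Report the treatment effect in each hospital, and the treatment-by-centre difference with its confidence interval, only for a contrast that both hospitals actually randomise. The comparator of the parallel trial must first be reconciled with PRE_NA; otherwise two different contrasts would be presented as one effect by centre.
4. State that the pooled conclusion applies to these two hospitals, and remove the statement that the model extends it to the centres concerned in any wider sense.

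The cost is wording only, with no new data or patients. The price is a more modest claim of generalizability.

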## Discussion

Total knee replacement is a surgical procedure with a high prevalence and associated health costs. The main objective is the elimination of pain and the maximization of the knee function. It is applied as the solution of severe osteoarthritis, a condition that greatly affects the proprioceptive system of the joint. The surgery involves greater deterioration, even when the posterior cruciate is preserved. Both the degeneration due to prolonged osteoarthritis and the procedure bears the consequence that, even after surgery, many limitations often persist [3, 4]. This bears a clinical impact on the balance abilities of the patient, which may be a direct cause of the functional limitations found [11, 12].

An early rehabilitation is essential, a continuous treatment when the subjects tolerate higher intensities is beneficial, and even when a muscular preconditioning is always recommended before any highly invasive surgery, there is still controversy about the effects in the total knee replacement outcomes. This is especially applicable if a cost-effective procedure is sought. For this reason, the use of a specific preoperative program have to be justified in economic terms, given the limitation of resources [7].

The design of this research will determine the effects and benefits of conducting training oriented towards balance and proprioception recovery, but also whether an in-home training can be as effective as a hospital supervised preparative training. While it is true that the inclusion of a control group renders the project implementation more arduous, it also makes it possible to determine the real effects of the experimental interventions. In addition, the costs of the in-home program are considerably lower than those of the hospital care. Therefore, a more cost-effective solution will be found if it is shown that in-home training achieves similar effects to the supervised one. The analysis will allow to ultimately conclude if, indeed, implementation costs are justified, and the proposal is applicable to clinical practice.

The design of the interventions has been realistic, and the information provided by clinicians with long experience and by the patient feedback has been fundamental. The experimental intervention at home (PRE_EXP2) has been designed to cover the basic aspects of the one performed in the hospital (PRE_EXP1). Certainly the possibilities of supervised work and hospital instrumentation are not available at home, but this has been taken into account and the adaptation of the intervention was made considering a pragmatic design.

Inclusion criteria are broad, not restricted to a large number of patients with comorbidities, which will increase the applicability of the proposal. The exclusion criteria have been proposed not to promote the results, but only for reasons of safety in the implementation of interventions. Therefore there is no exclusion due to social disadvantages, depression, anxiety or poor motivation, which are often frequent.

The trial began the recruitment of participants in March 2017. We expect to finalize the recruitment by June 2018. Early-postoperative outcome data are expected to be available from October 2018. Follow-up evaluations will be performed during 2019. The trial is expected to be completed by the end of 2019.

This work will serve as a basis for reducing implementation bias. In case of substantial changes in the protocol, they will be duly reported with the reasons.

It is necessary to recognize limitations such as the fact that the follow-up is prolonged beyond usual in clinical practice, and that some of the measures are not always used by clinicians, although they are indeed used in research. We plan to share, critically appraise and disseminate the results by offering critical discussion of the findings, description of potential clinical impact, clinical application, and contextualization within contemporary literature.

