Balance and proprioceptive approaches have been referred to as sensorimotor and neuromuscular trainings. A recent qualitative review suggested that these may be an acceptable adjunct to usual care in physiotherapy [13]. Nevertheless, the literature is scarce with respect to the impact of an additional training specifically oriented towards the recovery of balance and proprioception. Gstoettner et al. [5] suggested that balance and proprioceptive training is effective in improving standing balance, can avoid pathological gait patterns and falls, and proposed that further investigations were needed in order to give consistency to the findings. Later, Hubber et al. [14] and Villadsen et al. [15] evaluated the effects of a preoperative neuromuscular training program, while Fernandes et al. [16] analyzed the cost-effectiveness of the latter. None of them performed a comparative study between hospital and in-home intervention appraising the effects, pragmatism and costs.

With this background, this trial will determine the short and mid-term effects of a preoperative balance and proprioceptive training when conducted by patients undergoing total knee replacement, and the impact that this may have on the balance of the patient, functionality and quality of life [17]. Along with the effects, it is intended to determine whether in-home based training can be as effective as hospital training. The results will help to conclude whether the possible benefits may outweigh the health costs.

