### Sample size

A priori sample size estimation was made with the tool G*Power3.1 [20]. One-way ANOVA power analysis with three groups was based on the results of previous works [21]. The analysis considered that the groups receiving preoperative intervention will reach a score on the primary outcome the Berg Balance Scale of 53, this score being 5 points above that of the non-intervention group, with a reasonable standard deviation of 4.5 points, and with α = 0.05. The trial must consist of groups of 20 participants in order to achieve *d* > 0.8 and *f*
^2^ > 0.5. Predicting over 20% of sample loss, a total of 75 participants will be divided into 3 equal groups. Once data are collected, a post-hoc analysis will determine if the sample provided sufficient power to the trial.

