#### Economic evaluation

An economic analysis will be carried out to evaluate the cost-effectiveness of the experimental proposals versus the non-active comparator proposal. This will take into consideration all costs that are potentially related to each intervention, to the resources related to the training of the participant in the hospital, or in the case of performing the intervention at home, related to education and the time invested in monitoring the participant in order to ensure the compliance with the treatment. Appropriate unit costs will be allocated according to data from the national health system, including not only the time spent by physiotherapists but also by physicians [32].

The measure of effectiveness will be based on the results of the EuroQoL-5D, which will be used to estimate Quality Adjusted Life Years (QALY) estimated with the Spanish intervention rate associated with the time trade-off method. The analysis will be based on the mean overall cost and mean overall effect of each intervention. If a technique is less costly and more effective it will be deduced that it is cost-effective and therefore the one that will best optimize the use of resources. The acceptability curve will be plotted for the estimation of uncertainties. Finally a sensitivity analysis will allow to know the robustness.

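### The plan asks whether in-home training matches hospital training but states only tests of difference, so it has no valid criterion for concluding that the two are similar

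*Protocol article*

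**What the plan says.** The protocol article gives the home-versus-hospital question in its Abstract, Background and Discussion. In the Background, "it is intended to determine whether in-home based training can be as effective as hospital training"; in the Discussion, the design is to establish "whether an in-home training can be as effective as a hospital supervised preparative training". The Discussion then draws a consequence. Because home training costs less, "a more cost-effective solution will be found if it is shown that in-home training achieves similar effects to the supervised one".

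The Data analysis section plans an "ANOVA analysis of repeated measures, looking for interactions initially as a function of time, group, and time per group", with ANCOVA instead if baselines differ, followed by post-hoc analyses at the 95% level. Its one hypothesis is that the experimental groups will have better balance. It also plans Cohen's d, a post-hoc power calculation, and a check of change from baseline against published minimum important or detectable differences.

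The Sample size section says "One-way ANOVA power analysis with three groups was based on the results of previous works". It assumes that "the groups receiving preoperative intervention will reach a score on the primary outcome the Berg Balance Scale of 53". The untrained arm is placed 5 points lower, at 48. The other inputs are an SD of 4.5, alpha of 0.05, 20 per group, and 75 in total after loss.

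The Economic evaluation section sets out to "evaluate the cost-effectiveness of the experimental proposals versus the non-active comparator proposal".

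**The concern.** Whether one treatment is as good as another cannot be settled by a test whose null hypothesis is that they do not differ. Such a test can show that home training is worse or better. Failure to reject says only that the data did not separate the arms, and that happens more readily when the trial is small or noisy.

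The parts of the plan do not fit together here. The aim is similarity, the stated inference is difference, and the sample size contains nothing about this contrast, because both trained arms are placed at 53 and the planned home-hospital difference is zero. The other planned summaries do not fill the gap. The minimum-difference check concerns change from baseline rather than home minus hospital. Cohen's d and post-hoc power come with no threshold for calling the arms similar.

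At stake is a service decision, namely replacing supervised hospital sessions with cheaper home sessions. Without a stated criterion, that decision could be reached because the trial was too imprecise to see a loss of benefit.

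**Working it through.** **Inputs from the Sample size section.** Berg means 53, 53 and 48; SD 4.5; alpha 0.05 (taken as two-sided for pairwise tests); 20 evaluable per arm; 25 per arm before loss.

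**Assumptions, not in the document.** A home-training loss of 2.5 points (half of 5), used only as an illustration. A correlation r of 0.5 to 0.7 between baseline and outcome, for the adjusted figures.

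**1. The plan's own figure.** The mean of the three group means is 51.33. The standard deviation of the means about it is √[(1.67² + 1.67² + 3.33²)/3] = 2.357, so f = 2.357/4.5 = 0.524. One-way ANOVA (noncentral F) with 20 per group has 95.2% power, and 20 is the smallest group size reaching 95%. Allowing for 20% loss, 60/0.80 = 75. The design reproduces and is well powered for trained arms against control.

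**2. Precision for home minus hospital, unadjusted.** Half-width = t(0.975, 2n−2) × SD × √(2/n).
- n = 20: 2.024 × 4.5 × 0.3162 = 2.88 points, which is 58% of the 5-point benefit.
- n = 25 (no loss at all): 2.011 × 4.5 × 0.2828 = 2.56 points, or 51%.

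In either case an observed difference of exactly zero would leave a loss of 2.5 points inside the interval.

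**3. Precision with baseline adjustment.** The SD becomes 4.5 × √(1−r²): 3.90 for r = 0.5 and 3.21 for r = 0.7. At n = 20 the half-width is 2.49 and 2.06 points respectively, or 50% and 41% of the planned benefit.

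**4. How often a 2.5-point loss goes undetected.** Two-sided 5% two-sample t test, noncentrality 2.5/[SD × √(2/n)]. At n = 20 unadjusted this is 2.5/1.423 = 1.757, giving 40% power.

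| Analysis | Non-significant, n = 20 | Non-significant, n = 25 |
|---|---|---|
| Unadjusted | 60% | 51% |
| Adjusted, r = 0.5 | 49% | 40% |
| Adjusted, r = 0.6 | 43% | 33% |
| Adjusted, r = 0.7 | 33% | 23% |

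The n = 25 column assumes no loss, whereas the plan predicts more than 20%. A Tukey correction over the three pairs would lower unadjusted power from 40% to 27% at n = 20.

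**5. What a non-inferiority comparison could achieve.** One-sided 0.025, no true difference, power = Φ(margin/SE − 1.96). With an illustrative margin of 2.5 points:
- Unadjusted: 42% at n = 20 and 50% at n = 25.
- Adjusted with r = 0.6: 59% at n = 20 and 69% at n = 25.

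For 80% power, evaluable n per arm = 2 × [4.5 × (1.960 + 0.842)/margin]². This gives 51 for a margin of 2.5 (64 with 20% loss), 29 for 3.33, 80 for 2 and 115 for 1.67. With adjustment and a margin of 2.5, it falls to 39 (r = 0.5) or 26 (r = 0.7).

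All figures are for the Berg scale. The document gives no SD or expected benefit for KOOS-ADL.

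**The case against.** The strongest reply is that the document never says a p-value above 0.05 will be taken to mean the arms are equivalent. That is correct. A reader might infer it, since no other criterion is offered, but the Discussion is conditional on similar effects being shown, and effect sizes are also planned. What stands is narrower: the plan leaves that misreading open and gives nothing valid to put in its place.

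A second tempting inference is that the economic conclusion itself hangs on a non-significant Berg or KOOS test. The Economic evaluation section does not support this. It uses costs and EuroQoL-5D QALYs for each intervention, with an acceptability curve and a sensitivity analysis. The link to similar effects appears only in the Discussion sentence. The remaining gap is that the named comparisons are against the non-active arm, while the practical choice is between home and hospital.

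Third, the contrast may be called subordinate: the formal hypothesis and the sample size concern training against no training, and an article may leave a margin to a fuller document. An unwritten margin alone would indeed be no finding. But this article states the aim, the tests and the sizing, and these conflict. A later document could supply a margin, but not the precision of a trial sized on another contrast.

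Finally, the 60% figure is the unadjusted one. Adjustment improves matters appreciably, but the plan uses ANCOVA only if baseline differences appear, so both sets of figures belong in view.

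**Conclusion.** The concern holds as a mismatch between aim and method. The plan sets out to judge whether home training matches hospital training, states only tests of difference, and sizes the trial on another contrast. It therefore has no valid basis for a conclusion of similarity.

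On the plan's SD and group size alone, the unadjusted interval for home minus hospital extends about 2.9 Berg points either way at 20 per arm (2.6 at 25 with no loss), more than half of the planned benefit. Under an illustrative 2.5-point loss, the difference test would miss it in about 60% of trials unadjusted and 33% to 49% with adjustment, at 20 per arm. The 2.5 points and the correlations of 0.5 to 0.7 are assumptions; no corresponding statement can be made for KOOS-ADL. The trained-versus-control comparison is not affected.

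**What to change.** - **Data analysis.** Base the home-versus-hospital conclusion on the baseline-adjusted difference with its 95% confidence interval, for Berg and KOOS-ADL, at the two time points the plan emphasises (6 weeks and 1 year).
- **Margins.** Before unblinding, fix and justify a separate margin for each scale. For Berg it could be a fraction of the planned 5 points. That fraction cannot be carried over to KOOS-ADL, which needs a margin on its own 0 to 100 scale.
- **Decision rule.** Call home training as effective only if the interval excludes a loss beyond the margin and home training also beats PRE_NA. Otherwise report the comparison as inconclusive. State that similarity will not be inferred from p > 0.05.
- **Sample size.** Say that the trial was not sized for this contrast, and give the expected interval width.
- **Economic evaluation.** Add the incremental in-home versus in-hospital comparison, using the per-intervention costs and QALYs already planned.

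This needs no new visits or measurements, only work to justify two margins, added wording, the extra intervals and one more economic contrast. The real cost is that the claim becomes harder to reach. At the planned size the comparison will often be inconclusive even if the arms are truly equal, and the Discussion should be worded with that in mind.
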